### Outcomes

#### Primary and secondary outcomes and measurements

The primary outcome of the study is improvement in physical performance among older people assessed by ADL and IADL, grip strength and gait speed. Secondary outcomes will include body composition analysis using BIA along with other measurements consisting of pre-activity readiness for physical activity (PAR-Q+), Physical Activity Scale for the Elderly (PASE), quality of life (SF-12), Falls Efficacy Scale-International (FES-I), fear of falling, depression (GDS), cognitive function (MMSE), nutrition status (MNA) and oral health (GOHAI).

Adverse events will be monitored by the team at the end of each session. Every week participants will fill in a form to indicate if they developed pain, muscle soreness as well as significant injuries or a medical event that results in participant seeking medical attention from a healthcare professional. If participants develop any acute symptoms or any serious adverse events and their condition becomes too serious for the medical doctor in the research team to manage in a community setting, they will be immediately referred and brought to the nearest hospital.

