#### General health status

A face-to-face interview will be conducted to obtain information about participants’ demographics, medical history, falls history, falls efficacy scale (FES-I) [49], cognitive assessment (Mini Mental State Examination (MMSE)) [50], quality of life assessments (SF-12) [51,52], depressive symptoms (Geriatric Depression Scale (GDS) [53]), social support (DUKE Social Support Index [54] and Lubben Social Network Support-6 (LSNS-6) [55]), physical activity (Physical Activity Scale for the Elderly (PASE)) [56], pre-activity readiness questionnaire measured though PAR-Q+ questionnaire [57], stage of motivational readiness for change using the Physical Activity Stages of Change Questionnaire [58], activities of daily living (Katz-ADL) [59] and Lawton’s Instrumental Activities of Daily Living (IADL) [60], nutrition status (Mini Nutritional Assessment (MNA)) [61] and oral health (Geriatric Oral Health Assessment Index (GOHAI)) [62].

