### Sample size

The sample size has been estimated for the primary outcome of this study, that is, changes in physical function. The sample size calculation is estimated based on several measures of physical function including mobility, balance, stability (8-Foot Up and Go Test), aerobic endurance (6-minute walk test) and activities of daily living (ADL). In order to achieve 80% power to detect differences in the 8-Foot Up and Go Test, 6-minute walk test and ADL as previously reported [27,64,65], an individually randomised trial would require 45 participants per arm. With a hypothesised intra-cluster correlation coefficient (ICC) of 0.02 and a minimum of 20 participants recruited per cluster, the required sample size is 63 per arm. Assuming 30% loss to follow-up, 82 participants per arm or a minimum total of 164 participants will be required. To recruit at least 164 participants with a cluster size of approximately 21, it will be necessary to recruit 8 low-cost flats.

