### Statistical analysis

The study design provides for four assessments with study participants – at baseline, immediately post-intervention, three months and six months follow-up. Description of participants’ baseline characteristics will be reported by groups. Categorical variables will be summarised by frequencies and percentages. Continuous variables will be summarised by means and SD or non-parametric equivalents. The data analysis for this trial will be undertaken on an intention-to-treat (ITT) principle [66]. The continuous variable outcomes (immediately post-intervention, three months and six months) will be compared between groups using a generalised estimating equations and linear mixed effect models with adjustment for baseline covariates. Groups with dichotomous outcomes will be compared using logistic regression models. Baseline values will be entered as covariates. Statistical significance is set at p < 0.05 and mean 95% confidence intervals (CI) or differences in percentage between the two groups will be reported at the follow-up time points. Data will be entered and analysed with SPSS 22.0 (SPSS Inc., Chicago, IL, USA).

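### The single primary outcome is four unranked measures at three follow-ups, with no primary visit and no success rule, so its error rate is undefined

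*Protocol article*

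**What the plan says.** The article's section on primary and secondary outcomes states: "The primary outcome of the study is improvement in physical performance among older people assessed by ADL and IADL, grip strength and gait speed". It gives no composite, order or lead measure. The General health status section lists the Katz ADL scale and the Lawton IADL scale as separate instruments, so there are four measures, not three.

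The Statistical analysis section says: "The continuous variable outcomes (immediately post-intervention, three months and six months) will be compared between groups". It names generalised estimating equations and linear mixed models, and logistic regression for dichotomous outcomes. It adds that "Statistical significance is set at p < 0.05" and that confidence intervals or "differences in percentage between the two groups will be reported at the follow-up time points". None of the three follow-ups is called primary. No section says whether one, some or all of the measures must be positive.

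The Sample size section says that it is built on the primary outcome. It then uses the 8-Foot Up and Go, the 6-minute walk and ADL. Only ADL also appears in the primary outcome definition.

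**The concern.** A confirmatory trial needs to say in advance which result decides its main question. Here four measures and three visits are all candidates, and the text does not choose among them. A report could lead with whichever measure and visit turned out best and still be consistent with the protocol.

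This matters because the Discussion expects significant positive effects to serve as a model for health policy. A claim of improved physical performance that rests on one of many unranked comparisons has no known false-positive rate.

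**Working it through.** **1. Does another section identify the intended primary measure?** The sample size is the natural place to look.
- Design effect: 1 + (20 − 1) × 0.02 = 1.38.
- Per arm after clustering: 45 × 1.38 = 62.1, rounded up to 63.
- With the 30% allowance as the article applies it: 63 × 1.30 = 81.9, rounded up to 82, or 164 in total.

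The stated 63, 82 and 164 are therefore reproduced. The starting figure ("an individually randomised trial would require 45 participants per arm") cannot be re-derived, because no effect size or standard deviation is given. It covers three measures, two of them outside the primary outcome definition, so it does not single out one primary measure. The six-month follow-up in the design section is a duration and is not named as the primary time point.

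**2. Number of comparisons.** 4 measures × 3 follow-ups = 12. With one overall group effect per measure from a repeated-measures model, there are 4.

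**3. Error rate if any one positive result counted.** Inputs: level 0.05 per test (sidedness is not stated; two-sided assumed), no true effect on any measure, and each test holding its stated level.
- 12 independent tests: 1 − 0.95^12 = 46.0%.
- 4 independent tests: 1 − 0.95^4 = 18.5%.
- 12 independent tests, counting only false findings of benefit: 1 − 0.975^12 = 26.2%.

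The article gives no correlations. The range was therefore explored by simulating 12 correlated normal test statistics (300,000 draws per setting), with assumed correlations of 0 to 0.6 between measures and 0 to 0.9 between visits. Selected settings:

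| Between measures | Between visits | Any of 12, two-sided | Any of 12, benefit only | Any of 4 (one visit), two-sided |
|---|---|---|---|---|
| 0 | 0 | 46.0% | 26.2% | 18.5% |
| 0.2 | 0.5 | 40.5% | 21.3% | 18.0% |
| 0.3 | 0.7 | 34.9% | 17.7% | 17.4% |
| 0.5 | 0.8 | 28.5% | 14.3% | 15.5% |
| 0.6 | 0.9 | 22.8% | 11.5% | 14.4% |

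Over the whole grid, any of 12 two-sided runs from about 23% to 46%, benefit only from about 12% to 26%, and any of 4 from about 14% to 19%. The nominal rates are 5% two-sided and 2.5% for benefit.

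**4. Error rate if all four had to be positive at one named visit.** Under the same settings, the chance of four false findings of benefit is below 0.2%. There is no inflation.

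**5. Power cost of keeping four primary measures at one visit.** Holm's first step is 0.05 / 4 = 0.0125.
- The standardised difference implied by 45 per arm, 80% power and two-sided 0.05 (an assumption, since the article gives no effect) is (1.960 + 0.842) × √(2/45) = 0.59.
- At 0.0125 the critical value is 2.498. Power at 45 per arm is Φ(0.5906 × √(45/2) − 2.498) = Φ(0.304) ≈ 62%.
- Restoring 80% would need 64 per arm, or 64 × 1.38 = 88.3, rounded up to 89 after clustering, against 63 planned.

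**The case against.** The strongest reply is that the article contains no rule under which one positive result is enough. A reader might infer that such a rule applies and that the trial-wide false-positive rate is therefore 46%, or some fixed band below it. The text does not support that. It sets no success rule of either kind, and under an all-four rule the inflation disappears. The correlations behind any figure below 46% are also assumptions.

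Three further points have weight.
- Twelve tests is one reading. The longitudinal models could give one group effect per measure, and the visit-by-visit results are described as intervals or differences to be reported, not as separate primary hypotheses. However, the same sentence says that outcomes at the three follow-ups will be compared between groups, so the 12-test reading remains open.
- The outcome is improvement, so two-sided rejections overstate false claims of benefit. That roughly halves the rate, but the matching nominal rate is then 2.5%, not 5%.
- A multiplicity procedure could sit in an analysis plan that is not shown, so its absence here is no fault.

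These points limit the size of the finding but do not remove it. Which measure and which visit are primary is protocol content. The article does state its primary outcome, in a form that leaves both choices open.

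**Conclusion.** The concern holds as a badly fixed primary outcome. It does not hold as a demonstrated false-positive rate. Four unranked measures, three follow-ups, one threshold and no success rule leave the error rate of the primary conclusion undefined.

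The size depends on the rule that would eventually be applied. If any one of 12 results counted, it would be between about 23% and 46% two-sided. With one test per measure it would be about 14–19%, which is still roughly three to four times the nominal 5%. If all four were required at one visit, there would be no inflation. These figures rest on two-sided testing, assumed correlations and tests that hold their stated level. The need to name a measure and a visit does not depend on which figure in the range applies.

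**What to change.** Before any follow-up data are analysed, state in the outcomes section one primary measure and one primary visit, and make the other measures and visits secondary. Gait speed at six months is one reasonable example: it is measured at screening, at baseline and at every follow-up. It is not the only defensible choice. Because the sample size section gives no power for gait speed, choosing it means stating what the planned size can detect on that measure.

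If the sponsor wants all four measures to remain primary, name one primary visit and test the four there with Holm's procedure.

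Cost: a wording change to the protocol and the registry entry, and no new data. Fewer results can be headlined as primary. Under Holm, power for a single measure at the first step falls from 80% to about 62% at the planned size, under the assumed standardised difference of 0.59. The Study status section reports that screening and baseline are complete, so recovering that power with more participants would mean reopening recruitment. A single primary measure at a single visit avoids this loss.

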### Blinding

The exercise instructors and team members will be aware of the allocation of participants. However, all outcome measures will be collected by a blinded assessor, unaware of group allocation. Participants will be told not to inform the assessor of their intervention status.

### Sample size

The sample size has been estimated for the primary outcome of this study, that is, changes in physical function. The sample size calculation is estimated based on several measures of physical function including mobility, balance, stability (8-Foot Up and Go Test), aerobic endurance (6-minute walk test) and activities of daily living (ADL). In order to achieve 80% power to detect differences in the 8-Foot Up and Go Test, 6-minute walk test and ADL as previously reported [27,64,65], an individually randomised trial would require 45 participants per arm. With a hypothesised intra-cluster correlation coefficient (ICC) of 0.02 and a minimum of 20 participants recruited per cluster, the required sample size is 63 per arm. Assuming 30% loss to follow-up, 82 participants per arm or a minimum total of 164 participants will be required. To recruit at least 164 participants with a cluster size of approximately 21, it will be necessary to recruit 8 low-cost flats.

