### Eligibility screening

Individuals that agree to participate in the study will be requested for their written informed consent and subsequently be screened to see if they fit the inclusion criteria that is aged 60 years and older, residing in low-cost flats in the Klang Valley and living independently at home. The medical history including medications of each participant was interview-administered and recorded as part of the screening process. Exclusion criteria include older people who are already involved or participating in any structured exercise programme, cognitively impaired and having uncontrolled medical condition(s).

The screening will comprise six measurements and physical function tests to identify eligible older adults for the intervention trial. These measurements will include height, walking speed assessment (walking 4 meters unaided), grip strength (Jamar hand dynamometer), body composition analysis using a 4-point bioelectrical impedance analysis (BIA) equipment (TANITA TBF-300A, Tanita, Japan). Tokens in cash and/or kind including rice packs and household items will be given to participants during screening, baseline, intervention and follow-up measurements to encourage and retain participation.

Eligible participants for the CERgAS intervention trial must be willing and able to attend a one-hour session, twice each week for 6 weeks, have a walking speed slower than 1.24 m/s for females or slower than 1.33 m/s for males [48], not suffering from contraindications to exercise including unstable cardiovascular disease, uncontrolled chronic medical conditions, recent fractures and musculoskeletal diseases that would interfere with the safety and conduct of the intervention program. Once individuals have been assessed as being eligible to participate, they will be invited to attend a baseline data collection.

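### The 80% power is stated for the 8-Foot Up and Go, the 6-minute walk and ADL, so it has no stated basis for gait speed, grip strength or IADL, three of the four primary measures

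*Protocol article*

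**What the plan says.** All references are to the protocol article.

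- **Primary outcome** (Methods, Outcomes section): "The primary outcome of the study is improvement in physical performance among older people assessed by ADL and IADL, grip strength and gait speed". The four measures are not ranked.
- **Purpose of the calculation** (Sample size): "The sample size has been estimated for the primary outcome of this study, that is, changes in physical function".
- **Basis of the calculation** (Sample size): "In order to achieve 80% power to detect differences in the 8-Foot Up and Go Test, 6-minute walk test and ADL", with target differences taken from three cited sources and not reproduced. The result is that "an individually randomised trial would require 45 participants per arm". This is inflated to 63 per arm for clustering (ICC 0.02, 20 per flat) and to 82 per arm, 164 in total, for 30% loss.
- **Tests performed** (Eligibility screening): "These measurements will include height, walking speed assessment (walking 4 meters unaided), grip strength (Jamar hand dynamometer") and body composition by bioelectrical impedance. The Measurements section repeats the function tests already described at all four time points.
- **Analysis** (Statistical analysis): baseline values are covariates, significance is at p < 0.05, and 95% confidence intervals are reported.

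**The concern.** The Sample size section says that it sizes the trial for the primary outcome, and then sizes it on a different set of measures. Power belongs to a given difference and SD in a given measure. A target for a timed up-and-go test or a 6-minute walking distance supplies neither for 4-metre gait speed, grip strength or IADL, although all of them concern physical function.

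A reader who takes the section at its word will credit gait speed, grip strength and IADL with 80% power. Gait speed matters most here: it is an eligibility criterion, the Background argues for it, and the Discussion lists it among the expected benefits. If it shows no significant effect, the article gives no planned difference against which to judge that result.

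**Working it through.** **1. The two lists side by side**

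| Measure | Basis of the sample size | Primary outcome | Named elsewhere as measurement or outcome |
|---|---|---|---|
| ADL | yes | yes | yes |
| 8-Foot Up and Go | yes | no | no |
| 6-minute walk | yes | no | no |
| IADL | no | yes | yes |
| Grip strength | no | yes | yes |
| Gait speed | no | yes | yes |

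One of the four primary measures is a sizing measure, and three are not.

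**2. The plan's own figures**

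Inputs from the Sample size section: 45 per arm, ICC 0.02, 20 per flat, 30% loss.

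- Design effect: 1 + (20 − 1) × 0.02 = 1.38.
- Clustering: 45 × 1.38 = 62.1, rounded up to 63 per arm.
- Loss: 63 × 1.30 = 81.9, rounded up to 82 per arm, 164 in total.

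The chain reproduces from 45 onwards. (Multiplying by 1.30 rather than dividing by 0.70 is a separate matter.) The starting 45 cannot be rebuilt, because the article gives no difference or SD. No step uses an input for gait speed, grip strength or IADL.

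**3. What 45 per arm can detect**

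Assumptions: two-sided 5% (sidedness is not stated), 80% power, a plain two-group comparison of means, no baseline adjustment.

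- Normal approximation: d = (1.960 + 0.842) × √(2/45) = 0.59.
- t distribution on 88 degrees of freedom: d = 0.597.

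So the 80% figure would apply to a measure that was not sized only if its true standardised difference were about 0.6 SD.

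**4. Power at smaller differences**

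Effective 45 per arm, noncentrality d × √(45/2), t distribution on 88 degrees of freedom. The values of d are assumptions.

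| Assumed d | Power |
|---|---|
| 0.4 | 47% |
| 0.5 | 65% |
| 0.6 | 80% |
| 0.7 | 91% |

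**5. Is 45 a fair effective number after losses?**

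82 × 0.70 = 57.4 completers per arm, or 57.4/4 = 14.35 per flat. The design effect is then 1 + 13.35 × 0.02 = 1.267, and 57.4/1.267 = 45.3. At the plan's ICC and equal flat sizes, 45 is reasonable.

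**6. Effect of the planned baseline adjustment**

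Adjustment multiplies the detectable difference by about √(1 − r²), where r is the correlation between baseline and follow-up. The article gives no r. For an assumed r of 0.5, 0.60 × 0.866 = 0.52 SD. For an assumed r of 0.8, 0.60 × 0.60 = 0.36 SD.

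**The case against.** Four points can be made for the plan.

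- **An article condenses.** This excuses the absence of effect sizes and SDs. It does not excuse calling one set of measures primary while stating power for another in the name of the primary outcome. That is a contradiction within the text.
- **ADL is shared.** This stands: the basis is partly valid. It covers one measure of four.
- **The two tests may be performed after all.** A reader might infer that the trial never measures them. The article does not support that. Eligibility screening announces six measurements, introduces its list as inclusive, and names only four. What can be said is that the two tests are not listed as a measurement or outcome anywhere outside the Sample size section. Even if they are performed, they are not among the primary measures.
- **Power may be adequate anyway.** This stands. A reader might infer that the trial is underpowered for gait speed, grip strength or IADL, but nothing here shows it. The true effects are unknown, 45 may be the largest of several calculations, and step 6 shows that baseline adjustment could lower the detectable difference well below 0.6 SD. Turning 0.6 SD into metres per second would need an SD that the article does not give. The small number of flats also affects power, but that is a separate issue, which the Discussion partly acknowledges.

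It would also go too far to say that a null result could not be interpreted. The promised 95% confidence intervals will show which differences are excluded. What is missing is a planned difference to set them against.

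**Conclusion.** The concern holds in a limited form. The Sample size and Outcomes sections contradict each other: 80% power is claimed for the primary outcome but stated for two measures outside it and one within it. The claim has no stated basis for gait speed, grip strength or IADL.

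As to size, the figure would carry over to those three measures only at a true difference of about 0.6 SD. Power is about 65% at 0.5 SD and 47% at 0.4 SD. These figures rest on a two-sided 5% level, an effective 45 per arm at ICC 0.02, and no gain from baseline adjustment. The differences themselves are illustrations, not estimates. The conclusion is that the stated power is unsupported for three of the four primary measures, not that the trial is too small.

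**What to change.** Keep the number of participants as it is and reconcile the two sections.

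1. Limit the 80% statement to ADL. If the 8-Foot Up and Go and the 6-minute walk are in fact measured, list them as outcomes instead and say so under Measurements.
2. For each of gait speed, grip strength and IADL, state the minimum detectable difference in the measure's own units, at 8 flats and the expected number of completers. No one of them should be treated as the single primary measure, since the Outcomes section does not rank them.
3. Take the SDs from the pooled baseline data, which the Study status section reports as complete. Note that the eligibility cut-offs on walking speed (1.24 m/s for women, 1.33 m/s for men) truncate the baseline gait-speed distribution, so its SD may understate the SD at follow-up.
4. Use a range of ICCs around 0.02. An estimate from eight flats is too imprecise to serve as a single planning value.
5. Allow for the planned baseline adjustment, and state the assumed correlation.

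The cost is a recalculation from data already held and a rewritten paragraph, with no change to recruitment, data collection or analysis. The downside is that the stated detectable differences may look less favourable than the present 80% claim.

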### Randomisation and allocation concealment

Randomisation takes place at the cluster level, that is, the low-cost public subsidised flats, to avoid contamination. The eight housing projects will be randomised into the intervention arm (4 flats) and control arm (4 flats). The study statistician using a computer generated random number sequence will allocate the low-cost flats into the intervention and control group. The statistician using sealed envelopes will advise the study coordinator of the low-cost flats allocation. Allocation will be concealed from the research team recruiting the flats and participants, as randomisation will only take place after baseline measures have been accomplished.

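### The 80% power makes no allowance for having only four flats per arm; at the effect implied by 45 per arm, a comparison without baseline credit has about 66%

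*Protocol article*

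**What the plan says.** The Sample size section of the protocol article builds the target in four steps.

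- The starting point is a trial without clusters: "In order to achieve 80% power to detect differences in the 8-Foot Up and Go Test, 6-minute walk test and ADL", the article says "an individually randomised trial would require 45 participants per arm".
- Clustering enters once, as a multiplier: "With a hypothesised intra-cluster correlation coefficient (ICC) of 0.02 and a minimum of 20 participants recruited per cluster". This step raises the 45 to 63 in each arm.
- Attrition is added: "Assuming 30% loss to follow-up, 82 participants per arm or a minimum total of 164 participants will be required".
- The number of flats comes last, from headcount: "To recruit at least 164 participants with a cluster size of approximately 21, it will be necessary to recruit 8 low-cost flats".

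The section on randomisation and allocation concealment splits the eight flats four against four. The Statistical analysis section plans generalised estimating equations and linear mixed models, with baseline values as covariates, at a 0.05 significance level. The Discussion names the small number of clusters as a limitation, but links it to confounding and not to power.

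**The concern.** A design effect of 1 + (m − 1) × ICC converts a clustered sample into an equivalent number of independent participants. It leaves untouched the critical value used in the calculation for the individually randomised trial, which is about 1.96 to 1.99. When whole flats are randomised, the arm comparison is judged against variation between flats, and eight flats in two arms leave 8 − 2 = 6 degrees of freedom to estimate it. The critical value is then 2.447. No step of the article's calculation depends on the number of flats, so the 80% would have come out the same with four flats or forty.

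If the 80% is too high, a null result would be read against a chance of missing the planned effect of one in five, when under the assumptions below it is nearer one in three.

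**Working it through.** **Inputs from the article:** 80% power; 45 per arm; ICC 0.02; m = 20; 63 per arm; 30% loss; 82 per arm; 8 flats, 4 per arm; alpha 0.05.

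**Assumptions, not stated in the article:** alpha is two-sided; the 45 applies to one continuous outcome compared between two equal arms.

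**Step 1, the article's own chain.** Design effect = 1 + 19 × 0.02 = 1.38. 45 × 1.38 = 62.1, rounded up to 63. 63 × 1.3 = 81.9, rounded up to 82; 2 × 82 = 164. 164 / 21 = 7.8, so 8 flats. Every figure reproduces, so the question is one of method and not of arithmetic.

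**Step 2, the implied effect.** With noncentrality d × √(n/2), 80% power at n = 45 and 88 degrees of freedom requires d = 0.597 SD (noncentrality 2.833). A normal approximation gives 0.591 SD.

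**Step 3, power on 6 degrees of freedom at ICC 0.02.** Effective n = n / (1 + (m − 1) × 0.02); noncentrality = 0.597 × √(effective n / 2); power is from the non-central t with critical value 2.447.

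| Analysed per arm | Per flat | Design effect | Effective n | Noncentrality | Power |
|---|---|---|---|---|---|
| 62.1 (45 × 1.38) | 20 | 1.380 | 45.0 | 2.833 | 65.8% |
| 57.4 (82 less 30%) | 14.35 | 1.267 | 45.3 | 2.842 | 66.1% |
| 63 completers in 4 flats | 15.75 | 1.295 | 48.6 | 2.945 | 69.1% |
| 82 (no loss) | 20.5 | 1.390 | 59.0 | 3.243 | 77.1% |

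Using d = 0.591 lowers each figure by about one point. A simulation of a t-test on four against four flat means (400,000 runs, d = 0.591) gave 65.2% at 14.35 per flat and 68.2% at 15.75.

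**Step 4, detectable effect.** 80% power on 6 degrees of freedom requires a noncentrality of 3.367. At effective n = 45, d = 3.367 / √22.5 = 0.71 SD. The ratio (3.367 / 2.833)² = 1.41 is the factor by which the effective sample would have to grow to keep 0.60 SD.

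**Step 5, a larger ICC (0.05, an assumption).** With 57.4 completers per arm, the design effect is 1 + 13.35 × 0.05 = 1.668, effective n is 34.4 and power is 54.6%.

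**Step 6, keeping a normal reference.** Referring a 6-degree-of-freedom statistic to 1.96 retains about 80% nominal power, but the two-sided type I error becomes 9.8%.

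**Step 7, credit for baseline adjustment.** If adjustment multiplies the variance by 1 − r², both between and within flats, 80% requires 1 / (1 − r²) = 1.41, so r = √(1 − 1/1.413) = 0.54. With 57.4 completers at ICC 0.02, r = 0.5 gives 78%, 0.6 gives 84% and 0.7 gives 91%. At ICC 0.05 the effective n must rise from 34.4 to 45 × 1.413 = 63.6, so r = √(1 − 34.4/63.6) = 0.68. All of this applies only if the 45 did not already use the baseline.

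**The case against.** The strongest counter-argument is that the planned analysis is not the unadjusted one. The Statistical analysis section enters baseline values as covariates, and for physical function measures a baseline to follow-up correlation of 0.54 or more may be achievable. A reader might infer from the 6 degrees of freedom that no analysis holding type I error at 5% could have 80% power. The article does not support that, because Step 7 shows adjustment could close the gap at ICC 0.02. Equally, it does not show that the gap is closed. It states no correlation, and it sizes the trial on changes in physical function, so the 45 may already contain the baseline gain.

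A reader might also divide 57.4 completers by 1.38 (effective n 41.6) and conclude that power is only 62%. That pairs the design effect for 20 per flat with flats that have shrunk to 14.35. At the matching design effect of 1.267, effective n is 45.3 and power is 66%. Adding 30% rather than dividing by 0.7 does leave 57 and not 63 completers, but the smaller flats roughly offset this, so it is not the source of the shortfall.

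A small-sample correction may be left to an analysis plan that is not shown, and its absence here is no fault. That does not rescue the power statement, because a correction of this kind is what lowers the power.

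The reservation about effect size stands. The 0.60 SD is inferred, and three outcomes from three cited sources lie behind the 45. If 45 was the largest of three requirements, power for the other outcomes would be higher. If alpha were one-sided 0.05 throughout, power would be about 71%.

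**Conclusion.** The point holds in a conditional form. The 80% is a large-sample figure carried through a design effect, with no allowance for 6 between-flat degrees of freedom. Given two-sided 5% alpha, the implied effect of about 0.60 SD, ICC 0.02 and no credit for baseline adjustment, power is about 66% with the planned loss, 69% with 63 completers per arm and 77% with full retention. None of these reaches 80%. The effect detectable with 80% power is about 0.71 SD. At an assumed ICC of 0.05 with the planned loss, power is about 55%.

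The method gap is certain. The percentages depend on a back-solved effect and an assumed two-sided test, and should be quoted with those conditions.

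**What to change.** Restate the power in the Sample size section using a t reference on 6 degrees of freedom: about 66% for the assumed effect, or 80% for about 0.71 SD. Give the assumed difference, SD and sidedness so that the figure can be checked. If the planned baseline adjustment is to be credited, state the assumed baseline to follow-up correlation, say whether the 45 already used it, and show the resulting power. Present results at ICC 0.02 and 0.05. Baseline measurements are complete according to the Study status section, so the between-flat ICC at baseline can inform that range.

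The cost is a less favourable power statement, or an explicit assumption about the correlation. Recruitment, the number of flats and the conduct of the trial do not change.
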